## Method/design

Participants (*n* = 308) who have undergone complete excision of focal adenomyosis will be randomly assigned 1:1 to the treatment group (triptorelin acetate) or the control group. Patients will be recruited at 10 hospitals across mid-west China. All research units have been approved by the ethics committees. Every patient will sign an informed consent form prior to this study. This report follows the Standard Protocol Items: Recommendations for Interventional Trials (SPIRIT) guideline (Additional file 1).

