### Interventions

Eligible participants are assigned by simple randomization in a 1:1 ratio to a group receiving surgery only (group A) or to a group receiving surgery plus GnRH agonists (group B). The GnRH agonist is administered in the intervention group as a 3.75 mg intramuscular injection (Diphereline, Ipsen, France) on the first day of menstruation after surgery, then once every 4 weeks for six courses. The signs and symptoms of hypoestrogenism, including hot flushes, night sweats, sleep disorders, abnormal emotions and osteoporosis, could be caused by the GnRH agonist; these should be carefully evaluated and participants could be treated with tibolone 1.25 mg per day as add-back therapy to maintain serum estradiol at 30–50 pg/ml [17].

The intervention will be discontinued or modified if an intolerable adverse reaction occurs in group B. Color doppler ultrasonography and a steroid hormone test on the 3rd and 6th month after conservative surgery can help to monitor adherence. During the trial, other medications, such as steroid hormone or herbal medicine, or another intervention, such as levonorgestrel-releasing intrauterine system (LNG-IUS) will be prohibited.

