Treatment-related AE are monitored at each visit. The AE are any unfavorable medical occurrences associated with the subject’s participation in the research, whether or not considered related to the study intervention. Serious adverse events (SAE) are events that are temporally associated with the subject’s participation in research that meet any of the following criteria: death, events that are life-threatening or severely or permanently disabling, events requiring in-patient hospitalization or prolongation of existing hospitalization, or any events deemed as serious by the local principal investigator. The proportion of patients with AE will be compared at 36 months to determine whether there is a difference between the groups.

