**Fig. 1 Fig1:**
[figure not shown]
Flowchart of this study

Intention to treat, which is based on the initial treatment intent, will be used as a foundation in our analysis. Participants who begin the allocated treatment are part of the trial, whether they finish it or not. The characteristics at baseline will be compared between the control and intervention groups. Continuous data will be summarized by the mean and standard deviation and the Wilcoxon rank sum test will be used to identify differences in baseline characteristic between the two groups. Categorical data will be described by number and percentage, using the Pearson chi-square test to compare data from the two groups.

The primary outcome measure is the difference in the recurrence rate between group A and group B after 3 years of follow up, which will be analyzed by the Pearson chi-square test. For efficacy parameters, such as the score for pelvic pain and dysmenorrhea, menstrual blood loss, and the size of the uterus and the lesion, will be analyzed using generalized estimating equations (GEE) or mixed effects model repeated measures (MMRM) to account for correlation among these observations at different follow-up points.

The variables from secondary outcomes, including scores on the SF-36 and the FSFI, the pregnancy rate, and pregnancy outcomes, are calculated during 36 months of follow up using GEE or MMRM analysis to compare groups A and B to identify differences between groups at different time points. The number of participants with adverse events (AE) or serious adverse events (SAE) will be calculated in each arm and taken into final statistical testing.

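### The adverse-event monitoring sentence covers treatment-related events, while the definition and the between-arm comparison cover all events; ascertainment could differ by arm if sites follow the former

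*Protocol article*

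**What the plan says.** The article describes AE handling in four places.

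- **Collection.** The AE paragraph of Outcome and outcome assessments opens: "Treatment-related AE are monitored at each visit". Table 1 has one matching row, labelled *Side effects*, ticked at all seven follow-up visits (3 to 36 months) with no restriction by arm.
- **Definition.** The next sentence counts any unfavourable occurrence "whether or not considered related to the study intervention". The SAE (serious adverse event) definition also makes no reference to cause. It rests on timing, "events that are temporally associated with the subject’s participation in research", together with a list of seriousness criteria.
- **Comparison.** The paragraph ends: "The proportion of patients with AE will be compared at 36 months to determine whether there is a difference between the groups".
- **Analysis.** The Data analysis plan says "The number of participants with adverse events (AE) or serious adverse events (SAE) will be calculated in each arm" and takes these counts into the final testing.

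Two design facts matter. Participants "who have undergone complete excision of focal adenomyosis will be randomly assigned 1:1", so surgery comes before randomisation and the randomised difference is the drug. The Randomization section says that subjects and investigators learn the assignment.

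**The concern.** A between-arm comparison of AE proportions is interpretable only if both arms are asked about the same events in the same way. Here the sentence on what is monitored is narrower than the definition and the analysis. A site that follows it applies a relatedness filter when the event is collected. That filter acts unequally, because group A receives no trial drug and so cannot have an event related to it.

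Three things would follow:

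- The group A proportion would be too low, and the comparison would lean against triptorelin.
- Relatedness would be judged by people who know the arm. The Discussion accepts that lack of blinding may cause substantial bias.
- An excess of events in group B that nobody linked to the drug would not be recorded, although a randomised all-event comparison is meant to detect exactly that.

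Events not recorded at a visit may not be recoverable at analysis.

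**Working it through.** The article states no AE rate, AE power or AE sample size, so there is no figure to reproduce. The check is mainly textual.

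**Step 1: the scopes side by side**

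| Element | Place | Scope |
|---|---|---|
| Monitoring sentence | Outcome and outcome assessments | treatment-related |
| Schedule row *Side effects* | Table 1 | suggests drug effects; no arm restriction |
| AE definition | Outcome and outcome assessments | any, related or not |
| SAE definition | Outcome and outcome assessments | temporal association |
| Comparison at 36 months | Outcome and outcome assessments | AE, unrestricted |
| Counts for testing | Data analysis plan | AE and SAE, unrestricted |

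The first row conflicts with the last four. The second leans the same way as the first.

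**Step 2: what treatment means**

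- *For the narrow reading:* Method/design calls group B the treatment group, with triptorelin acetate in brackets, as opposed to the control group. Background and Discussion use the term side effects for effects of medicines. Surgery precedes randomisation.
- *For the wide reading:* Interventions describes group A as receiving surgery. Outcome and outcome assessments speaks of pregnancy outcomes in each treatment arm. The Data analysis plan speaks of participants starting their allocated treatment, whichever it is.

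Both readings are available, and the article does not settle between them.

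**Step 3: sensitivity if the narrow reading were followed (illustration only)**

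Inputs: 308 participants from Sample size calculation, so 308/2 = 154 per arm on average. *Assumed, not in the article:* group A records 0; the drug has no true effect; the background AE rate q is the same in both arms (10% to 40%); a share f of group B's events (10% to 50%) is attributed to the drug and recorded.

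For 0 v k with n per arm, the uncorrected Pearson statistic is 2nk/(2n − k), and the two-sided Fisher p is 2·C(n,k)/C(2n,k).

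- k = 4 (4/154 = 2.6%): 308 × 4/304 = 4.05, p = 0.044; Fisher p = 0.12.
- k = 6 (6/154 = 3.9%): 308 × 6/302 = 6.12, p = 0.013; Fisher p = 0.030.

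The smallest count reaching p < 0.05 is 4 by Pearson (k = 3 gives p = 0.082) and 6 by Fisher (k = 5 gives p = 0.060). The chance of a falsely significant result is therefore P(X ≥ 4) or P(X ≥ 6), with X binomial(154, q·f):

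| q | f | recorded A v B | Pearson | Fisher |
|---|---|---|---|---|
| 10% | 10% | 0 v 1% | 7% | 0.5% |
| 10% | 50% | 0 v 5% | 95% | 79% |
| 30% | 10% | 0 v 3% | 68% | 32% |
| 30% | 25% | 0 v 7.5% | 99.8% | 98% |
| 40% | 50% | 0 v 20% | about 100% | about 100% |

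With equal all-event recording, both arms would show q and the error rate would be about the nominal 5%. The spread from under 1% to about 100% shows that the result is driven by assumptions the article does not supply.

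**The case against.** The strongest reply is that this is one loose adjective. The AE definition, the SAE definition, the comparison and the analysis plan all use the all-event scope, and the comparison uses the defined term. Table 1 schedules its row for both arms, including visits well after the injections end. Collection is by a standard case report form that is not shown, and Data collection commits generally to ICH-GCP.

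Much of this stands. A reader might infer that the protocol records nothing but treatment-related events, so that group A is near zero by construction. The text does not support that. It contains no word such as *only* and no statement that unrelated events go unrecorded. The near-zero result also needs treatment to mean triptorelin alone, while the article uses the word for both arms, so surgery-related events in group A could count. What sites actually record cannot be known without the form.

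The p-values are open to the same objection. The zero in group A is an assumption, and with 0 v 4 significance depends on the test chosen.

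What the reply does not remove is the conflict itself. Both scopes are printed in adjacent sentences, so this is not detail left to a fuller document. A general commitment to good practice does not tell a site which sentence governs. An unrestricted row also helps little if control patients are asked about side effects of a drug they did not receive.

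**Conclusion.** The concern holds as an internal inconsistency with a conditional consequence. The monitoring sentence, and to a lesser degree the Table 1 label, are narrower than the AE definition and the planned between-arm comparison. If sites follow that sentence and read treatment as the drug, group A's proportion will be artificially low, and the comparison will be biased against triptorelin and blind to unattributed excess events.

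The direction of that bias is clear. Its size is not: the article gives no AE rate, and the figures above rest on an assumed zero in group A and assumed ranges for q and f. They show that a handful of recorded events could decide the test, not that the planned comparison is biased. A claim that the design guarantees such bias would go beyond the text. The point concerns one secondary safety outcome and leaves the primary analysis untouched, but it should be corrected because the cost is small.

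**What to change.** - **Monitoring sentence.** Replace with: *All AE, whether or not considered related, are recorded at each visit in the same way in both groups, with relatedness recorded as an attribute.*
- **Table 1.** Rename the row *Adverse events*.
- **Comparison.** State that the between-group comparison uses all AE and all SAE, and that drug-related events in group B are reported descriptively.
- **Participants already enrolled.** More than 90 had been enrolled when the article was written. Check which scope the case report form has applied so far, and report it if it was the narrow one.

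The cost is one sentence, one label and a reminder to sites. The downside is slightly more event recording in group A. No treatment changes.

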### Data analysis

#### Sample size calculation

Sample size was determined based on data from a prospective study demonstrating a relapse rate of about 49% in the group that received surgery alone and 28.1% in the group that received surgery and GnRH agonist treatment [7]. A two-tailed test with alpha set at 0.05 and 85% power is used to detect a minimum clinically meaningful difference between control and intervention groups. The minimal sample size is calculated as 139 participants in each group. In consideration of a dropout rate of 10%, we will recruit 308 participants in total.

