## Discussion

The preservation of fertility and the integrity of the reproductive organs is increasingly of concern to women with adenomyosis. Due to the disadvantage of medical treatments, adenomyomectomy was now increasingly applied. Remission from dysmenorrhea or dyspareunia after complete excision of the lesion has been reported as 50–94.7% and improvement in menorrhagia as 25–80% [18]. Nevertheless, a symptomatic or local recurrence of the condition may occur. About 2.8–13.95% of patients relapsed at the end of first year in this study; 14.28–49% of patients had recurrence of disease in the following 24 months [18]. Therefore, the long-term management after surgery is the main issue to be addressed.

Recently, AI Jama retrospectively analyzed 18 patients who underwent adenomyomectomy and treatment with GnRHa for 24 weeks, 15 of whom had systematic improvement after 1 year of follow up [16]. Liu carried out a non-controlled descriptive study of 186 women with pathologically proven adenomyoma, who underwent ultramini-laparoscopic adenomyomectomy and a 6-month course of goserelin acetate treatment. The rate of systematic recurrence was 9% after 3 years of follow up [19]. Wang et al. identified a significant decline in the relapse rate in the surgical-medical treatment group at the end of 2-year follow up in a prospective, non-randomized study [7]. However, our retrospective analysis showed no difference between the control and intervention group at the end of the first or second year. It is noteworthy that there was a significant difference between the control and the GnRH agonist group in symptomatic relapse or relapse as identified on imaging studies at the end of the 36-months follow up. In other words, postoperative treatment might be applied to reduce the long-term recurrence rate. Whether or not we should use the postoperative method to prevent relapse in patients with adenomyosis is still unknown.

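### The stated 139 per group does not follow from 49% v 28.1% at 85% power, which needs about 96; 139 gives about 95% power for those rates

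*Protocol article*

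**What the plan says.** The Sample size calculation section of the protocol article takes its rates from an earlier prospective study: "a relapse rate of about 49% in the group that received surgery alone" and "28.1% in the group that received surgery and GnRH agonist treatment". It then says: "A two-tailed test with alpha set at 0.05 and 85% power is used to detect a minimum clinically meaningful difference". That difference is given no number of its own. The result is: "The minimal sample size is calculated as 139 participants in each group". A 10% dropout allowance follows and brings the total to 308.

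Two other sections fix the setting. Method/design gives 1:1 allocation. The Data analysis plan compares recurrence after 3 years of follow-up by the Pearson chi-square test. The Discussion describes the study that supplied the rates (the same reference number) as showing a "significant decline in the relapse rate in the surgical-medical treatment group at the end of 2-year follow up in a prospective, non-randomized study".

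**The concern.** The paragraph gives every input of a two-proportion calculation as well as its output, so the output can be checked, and it does not come out. If the rates, alpha and power are right, 139 is not the minimum. If 139 is right, the power or the target difference is not the one a reader takes from the text.

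This bears on how the result is read. At 139 per group the trial has about 95% power for a 20.9-point difference, or about 85% power for roughly 17.5 points. A non-significant result speaks against different effects in the two cases. This is the only sample size justification in the article, and it concerns the primary outcome.

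A smaller point belongs in the same paragraph. The rates come from a study with 2-year follow-up and the primary comparison is at 3 years. The paragraph does not say that the rates are assumed to carry over.

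**Working it through.** **Inputs.** p1 = 0.49, p2 = 0.281, two-sided alpha 0.05 and power 0.85 (Sample size calculation); 1:1 allocation (Method/design); Pearson chi-square (Data analysis plan). Hence d = 0.209, mean rate p̄ = (0.49 + 0.281)/2 = 0.3855, z(0.975) = 1.960 and z(0.85) = 1.036.

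**Attempt to reproduce 139.** The pooled formula, which matches the chi-square test, is

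n = [z(0.975)·√(2p̄(1−p̄)) + z(0.85)·√(p1(1−p1) + p2(1−p2))]² / d²

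- √(2 × 0.3855 × 0.6145) = 0.6883
- √(0.2499 + 0.2020) = 0.6723
- n = (1.960 × 0.6883 + 1.036 × 0.6723)² / 0.0437 = 95.8, so 96 per group

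Other standard choices with the same alpha and power:

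| Method | n per group |
|---|---|
| Unpooled variance | 93 |
| Arcsine | 96 |
| Simple pooled variance | 98 |
| Continuity-corrected | 106 |
| Fisher exact | about 104 |
| Log-rank, Schoenfeld | about 92 |
| Log-rank, Freedman | about 100 |

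A one-sided test at 0.05 would need fewer still (77). The stated 139 is 45% above 96 (139/96 = 1.45) and 31% above 106 (139/106 = 1.31).

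**Is dropout already inside 139?** No. It is added afterwards: 2 × 139 = 278, and 278/0.9 = 308.9, against 308 stated. That step is consistent, apart from rounding. Dropout on 96 would give 96/0.9, so 107 per group. The paragraph states no other inflation.

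**Power at 139 per group for 49% v 28.1%.**

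power = Φ{[d − 1.960·√(2p̄(1−p̄)/n)] / √([p1(1−p1) + p2(1−p2)]/n)}

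= Φ{(0.209 − 1.960 × 0.0584)/0.0570} = Φ(1.66) = 95.1%

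Exact enumeration of the chi-square test gives 95.2%; the continuity-corrected test gives 93.7% and Fisher's test 93.9%.

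**Which settings do give about 139?** Each one changes or adds an input:

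| Setting | n per group |
|---|---|
| 49% v 28.1%, two-sided 0.05, 95% power | 138 pooled, 139 arcsine |
| 49% v 28.1%, two-sided 0.01, 85% power | 140 pooled, 139 arcsine |
| 49% v 31.5% (17.5 points), two-sided 0.05, 85% power | about 139 (84.9% power at 139) |
| 45.3% v 28.1% (17.2 points), two-sided 0.05, 85% power | about 139 (84.9% power at 139) |

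The arithmetic cannot say which of these, if any, was used.

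**The case against.** The strongest defence is that the paragraph speaks of a minimum clinically meaningful difference without giving it a number, and never says that it equals the 20.9 points between the two quoted rates. If a smaller target of about 17.5 points was used, 139 at 85% power is correct and only the target is missing. This stands as a possible explanation. It does not clear the paragraph, because the only rates given do not lead to the number given. It does limit the fix: the phrase should not simply be deleted, since it may be the real basis of the design. For the same reason, a reader who infers that the article declares 20.9 points to be the smallest worthwhile effect goes beyond the text.

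The second defence is that the error is on the safe side. That is correct. Under the stated rates the trial is larger than needed, and no test, alpha level or decision rule changes.

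Two stronger readings are tempting, and the article supports neither.

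- A reader might infer that the team's own data contradict the assumed effect, because the Discussion reports that "our retrospective analysis showed no difference between the control and intervention group at the end of the first or second year". The next sentence there reports a significant difference at 36 months, which is the primary time point. Taken whole, the passage supports the choice of time point.
- A reader might infer that the trial is underpowered because the 3-year control rate could be below 49%, the top of the 14.28–49% range quoted in the Discussion. A lower rate is possible. But the Discussion's figures rise with time (2.8–13.95% at one year, 14.28–49% over the following 24 months), so moving from 2 to 3 years in the same population would tend to raise the rate. Holding the planned risk ratio (0.281/0.49 = 0.573), 139 per group gives about 80% power at a 35% control rate but about 98% at 55%. Scenarios in one direction only would mislead, and neither direction bears on the arithmetic.

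Planning from an observed difference in a non-randomised study is common, and the article discloses the design of that study. It is not a fault in itself.

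**Conclusion.** The point holds as an internal inconsistency. With 49% v 28.1%, two-sided alpha 0.05 and 85% power, about 96 per group are required (93 to 106 across the unpooled, pooled and continuity-corrected formulas), not 139. With 139 evaluable per group, power for those rates is about 95%.

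This assumes that the two quoted rates are the planning target, that allocation is 1:1, and that no inflation was applied before the dropout step; the article mentions none. If a smaller difference was the target, the defect is that it is not stated.

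The discrepancy is conservative. It does not make the trial underpowered under its stated assumptions, and it gives no reason to change the 308. That the 2-year planning rates apply to the 3-year endpoint is an unstated assumption that should be made explicit; it is not an error of calculation.

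**What to change.** Retrieve the original calculation and rewrite the paragraph with the inputs actually used.

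- If the target was 49% v 28.1%, state the power at 139 evaluable per group as about 95%.
- If a smaller minimum clinically meaningful difference was used at 85% power, state it with both rates (for example 49% v 31.5%, about 17.5 points).
- If a different alpha or an inflation factor was used, state that.

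Add one sentence saying that 49% and 28.1% come from a non-randomised study with 2-year follow-up and are assumed to apply to the 3-year primary endpoint.

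The cost is the wording of one paragraph. The recruitment target stays at 308 and no other part of the design changes.

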### Randomization

Eligible participants are assigned by simple randomization in a 1:1 ratio to one of two groups. The sequence of randomization has been set up by biostatisticians in the data coordination center using Microsoft Excel and the “RAND ()” function. The original sequence is safely kept by the staff in the data coordination center, and it has been put into the online central randomization system by these staff members, who are not involved in enrolling subjects. The sequence is not accessible to any investigators or study coordinators. If a subject fulfills the enrollment criteria, the authorized study coordinator will obtain the assignment for her. After randomization, both subjects and investigators are informed about the assignments.

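### The stated 139 per group does not follow from 49% v 28.1%, two-sided 0.05 and 85% power: those inputs need 96 (106 with continuity correction), and 139 gives 95% power

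*Protocol article*

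**What the plan says.** All the design figures stand in the Sample size calculation section of the protocol article. It cites a prospective study with "a relapse rate of about 49% in the group that received surgery alone" and "28.1% in the group that received surgery and GnRH agonist treatment". It then sets the operating characteristics: "A two-tailed test with alpha set at 0.05 and 85% power is used to detect a minimum clinically meaningful difference" between the groups. The result is given as "The minimal sample size is calculated as 139 participants in each group", followed by "In consideration of a dropout rate of 10%, we will recruit 308 participants in total".

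Two other sections complete the inputs. The Randomization section gives equal allocation: "Eligible participants are assigned by simple randomization in a 1:1 ratio to one of two groups". The Data analysis plan section names the Pearson chi-square test for the primary comparison of recurrence rates after 3 years. The article states no other effect size, continuity correction, multiplicity adjustment or design factor.

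**The concern.** The article prints every quantity that a two-proportion sample size needs, so 139 should be reproducible from it. It exceeds the ordinary result by 43 women per group (139 against 96, or 45%), which is far too much for rounding or for the choice of formula.

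The stated power and target difference tell readers what the trial was built to detect. As written, they are told that it has 85% power for a 20.9-point difference. On its own rates it has about 95%, and its 85% power applies to a smaller difference. There is also an ambiguity about the test itself: 139 is close to what a two-sided alpha of 0.01 with 85% power would need. If that was the source, the significance level printed for the primary test would be the wrong item.

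**Working it through.** **Inputs.** p1 = 0.49, p2 = 0.281, two-sided alpha 0.05, power 85% (Sample size calculation); 1:1 allocation (Randomization); Pearson chi-square (Data analysis plan). Derived: d = 0.49 − 0.281 = 0.209 and d² = 0.043681; mean rate 0.3855; normal quantiles 1.960 and 1.036.

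**Step 1. Attempt to reproduce 139 with the formula that matches the test (pooled variance under the null).**

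n = [z(0.975) × √(2 × p̄ × (1 − p̄)) + z(0.85) × √(p1(1 − p1) + p2(1 − p2))]² / d²

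- √(2 × 0.3855 × 0.6145) = √0.47378 = 0.6883
- √(0.2499 + 0.2020) = √0.4519 = 0.6723
- n = (1.960 × 0.6883 + 1.036 × 0.6723)² / 0.043681 = (1.349 + 0.697)² / 0.043681 = 95.8, so **96 per group**

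The figure of 139 is not reproduced.

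**Step 2. Other standard methods at the same inputs.**

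| Method | n per group |
|---|---|
| Unpooled variance | 93 |
| Pooled variance | 96 |
| Arcsine | 96 |
| Continuity-corrected | 106 |
| Fisher exact | about 104 |
| Log-rank, Schoenfeld to Freedman | about 92 to 100 |
| One-sided 0.05 (with correction) | 77 (86) |

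The continuity-corrected value is (95.8 / 4) × [1 + √(1 + 4 / (95.8 × 0.209))]² = 105.2, so 106. It is the largest in the table and is still 24% below 139 (33 / 139).

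**Step 3. Power at 139 per group for 49% v 28.1%.**

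z = (0.209 × √139 − 1.349) / 0.6723 = (2.464 − 1.349) / 0.6723 = 1.659, which gives 95.1%. Exact chi-square power is 95.2%. With continuity correction it is 93.7%, and with Fisher's exact test 93.9%.

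**Step 4. Which single change brings n to about 139?**

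| Change | n per group |
|---|---|
| Power 95% | 138 (arcsine 139) |
| Two-sided alpha 0.01, power 85% | 140 |
| Intervention rate 31.5% | 140 |
| Control rate 45.5% | 137 |

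Power of 95% is the simplest candidate, but the text cannot separate these. Solving for the intervention rate at exactly 139 per group and 85% power gives 31.47%, a difference of 49 − 31.5 = 17.5 points.

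**Step 5. Dropout.** 2 × 139 / 0.9 = 308.9, and 139 / 0.9 = 154.4 per group; 2 × 154 = 308. The total follows from 139 to within rounding, so the dropout step is not where the mismatch arises. Nor can dropout already be inside the 139: even the continuity-corrected 106 becomes only 118 after division by 0.9.

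**The case against.** The strongest defence is that the section never says the observed difference was the target. It says the trial is sized "to detect a minimum clinically meaningful difference between control and intervention groups", and no number is attached to that phrase. If the planners chose a target somewhat below 20.9 points, alpha and power could both be as printed: about 17.5 points at 85% power gives 139 to 140 per group. That is possible. It does not make the statement reproducible, though, because the only rates printed would then not be the rates used, and the difference that fixed the size of the trial would be absent.

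A second defence is that the control rate is given only approximately. It would have to be about 45.5% to yield roughly 139, and rounding does not cover 3.5 points.

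Third, the error is conservative. If the cited rates hold, the trial has more power than claimed, no analysis changes, and a null result will be judged mainly on the confidence interval. Recruitment was also expected to finish in late 2019, before the article appeared. All of this stands and lowers the urgency. It does not make the printed statement correct.

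Finally, 95% should not simply be written in as if it had been the plan. It depends on rates from a study that the Discussion describes as non-randomized with 2-year follow-up, whereas the primary comparison here is at 3 years. That bears on how the correction is worded, and the fix takes it up.

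**Conclusion.** The concern holds. From the stated inputs the planned test needs 96 women per group, or 106 with continuity correction, against the stated 139. At 139 per group the power for 49% v 28.1% is 95% (about 94% with continuity correction or Fisher's exact test), not 85%. With 10% dropout the stated inputs would need 107 per group (96 / 0.9 = 106.7), or 214 in total, against 308.

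Either the power or another printed input (the alpha or the relapse rates) is not the one used, and the article does not allow a reader to tell which. The power figures assume the cited relapse rates, 1:1 allocation and 139 evaluable women per group. The trial is not underpowered on its own assumptions; what is wrong is the published justification of its size.

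**What to change.** 1. Trace the original calculation (software output or worksheet) and establish whether the power, the alpha or the target rates were misreported.
2. Correct the Sample size calculation section so that rates, alpha, power and n agree. If a target smaller than 20.9 points was used, state it.
3. If the original cannot be found, say so and report what the design delivers, labelled as conditional on the cited rates. Suggested wording: *With 139 evaluable women per group, a two-sided 0.05 chi-square test has 95% power for 49% v 28.1%, and 85% power for 49% v 31.5% (17.5 points).*
4. Carry the same statement into the SAP, if it repeats the calculation, and into the results paper.

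Keep 308: after 10% dropout it leaves about 138 per group, and power is still 95%. The cost is a check of the file and one corrected sentence, with no added patients and no change to the analysis. The exception is if tracing shows that alpha 0.01 was intended; the significance level for the primary test would then have to be settled before the data are analysed.
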